#### Economic evaluation

Economic evaluation methods will, as far as possible, adhere to the recommendations of the NICE Reference Case [46]. The economic evaluation will consist of a within-trial analysis and economic modeling. Within trial analysis will compare direct costs and 18-month outcomes of patients randomized to intervention versus control. The primary perspective adopted will be that of direct NHS and patient costs. A costing study will record intervention costs (to include staff time, capital, overheads and consumables), other NHS resource use (for example, GP visits, hospital visits, and admissions) and selected patient expenditure. Unit costs for health care resources will be derived from local and national sources and performed in line with best practice [47]. Costs will be standardized to current prices where possible. Because of the short follow-up period, we will not discount costs or benefits.

Comparison will be made between baseline and follow-up to estimate incremental cost-effectiveness ratios (ICERs) comparing the intervention with the control group in terms of the primary outcome measure (patients achieving all three clinical targets) and costs [40]. Quality of life (EQ-5D) over the study period will be used to generate quality-adjusted life-years (QALYs) [48]. Outputs will be presented as ICERs, cost-effectiveness acceptability curves and expected net benefit. Sensitivity analyses will consider key cost drivers and factors that might affect the outcomes measured in order to explore uncertainty in the conclusions drawn.

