Practices recruited to the study are randomized to either usual care or intervention arm, with the latter having access to the new ICCD clinics. In participating practices, patients with T2DM are invited to take part in the trial. Recruited patients in both arms are given a baseline assessment by a study nurse. This includes measurement of HbA_1c_, body mass index (BMI), waist circumference, blood pressure, urine and lipids. Participating patients are asked to attend a follow-up assessment 18 months after their baseline assessments, when the same measurements are repeated. Questionnaires about quality of life, satisfaction with current services, continuity of care and health service use and personal costs are completed at baseline and follow-up. An integral economic evaluation measures costs in both groups, with a comparative assessment of marginal costs and outcomes. To deal with possible selection bias, risk factor control of all patients with T2DM in intervention and control practices will be compared using anonymised GP data. Additionally, a qualitative study is exploring the views of patients, health professionals and other stakeholders using semi-structured interviews.

The overall aim is to conduct a randomized controlled trial to evaluate the effectiveness and cost-effectiveness of community-based intermediate care clinics in the management of T2DM. Specific objectives are to:

1. Compare the following in patients with T2DM registered with practices that have access to ICCD with those that have access only to usual care:

·control of cardiovascular risk factors including glycemic, blood pressure and lipid control, and cardiovascular risk assessed by UKPDS risk engine;

·quality of life;

·satisfaction with services and continuity of care;

·referral patterns and non attendance rates;

·annual cost per patient with diabetes.

2. Estimate the difference in the cost of the resources used by patients in each arm of the trial, and the cost-effectiveness of the ICCD intervention.

3. Explore the views and experiences of patients, health professionals and other stakeholders.

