#### Economic outcome measures

Data on NHS resource use and personal costs to patients are being collected using standard measures for economic analysis [40]. Direct NHS costs include the number of referrals to and attendances at ICCD in the intervention arm and to hospital in the control arm. We are also recording the number of GP, practice nurse, optometrist, podiatrist and dietician consultations, and total hospital attendances, which include both inpatient and outpatient visits. Data are also being collected on prescribed medication and tests linked to diabetes, including diabetic retinopathy tests. For patients who are referred to ICCD, we note the number of contacts with professionals, as well as any group or educational intervention. Direct personal cost data include personal expenditure such as travel costs and indirect costs such as days off sick from work or reduced hours of employment are being collected. These data are obtained at the time of the follow-up assessment.

Impact on health utility will be assessed using the EQ-5D questionnaire [35,41]. Comparing this with costs (directly and indirectly related to patient management) will enable incremental cost-effectiveness of the intervention to be estimated.

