### Analysis

#### Statistical analysis

Intention-to-treat (ITT) comparisons of the two groups will be conducted, with the primary dependent variable being the proportion of patients achieving all three clinical targets at 18 months. The main analysis will be based on all patients recruited to the study. As some drop-outs and losses are inevitable, sensitivity style analyses are planned. Missing data imputation will use ‘last observation carried forward’ (LOCF). Secondary analyses will exclude all observations with missing values. Analyses will use a mixed effects logistic regression model, and will adjust for baseline characteristics at both practice and individual level. The former may include practice size and deprivation index, and the latter age, gender, BMI, ethnicity, employment status, educational level and length of time since diagnosis. Characteristics will be included using a forward selection model-building strategy, with only variables significant at the 10% level selected. Odds ratios (OR) will be estimated with 95% confidence intervals, adjusting for potential confounding variables and allowing for the effect of the cluster randomization [43].

Further analysis will examine secondary outcomes (achievement of individual targets for blood pressure, HbA1c and lipids), again adjusting for confounders and allowing for the cluster randomization. In addition, UKPDS 10-year risk scores for CHD and stroke will be analyzed using a linear mixed model.

Tertiary analysis of questionnaire responses will consider longitudinal continuity, flexible continuity, relational continuity and term and boundary continuity following the NCCSDO methodology on ‘continuity of care in type 2 diabetes’ [44]. We will also compare the levels of ICCD use by the intervention practices, and the drop-out rates for all practices.

Finally, all analyses will be re-run with added data from MIQUEST covering all diabetes patients in a practice whether recruited to the trial or not [45]. This will lessen the number of variables available, but otherwise all analyses for primary and secondary endpoints will be repeated.

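### If the LOCF primary result feeds the ICER, lost patients dilute the effect but not the cost: about 1.25 times too high at the implied 20% loss, under stated assumptions

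*Protocol article*

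**What the plan says.** **Effect side.** The Statistical analysis section states: "The main analysis will be based on all patients recruited to the study". For missing values it says: "Missing data imputation will use ‘last observation carried forward’ (LOCF". A complete-case analysis comes second: "Secondary analyses will exclude all observations with missing values". The Background gives two assessments only: "Participating patients are asked to attend a follow-up assessment 18 months after their baseline assessments, when the same measurements are repeated". The opening of the Outcome measures section places the baseline assessments before randomization and before the clinics were launched.

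**Ratio.** The Economic evaluation section builds the ICER "in terms of the primary outcome measure (patients achieving all three clinical targets) and costs", by comparing baseline with follow-up. It derives QALYs from the EQ-5D, and it will report ICERs, acceptability curves and expected net benefit. It names one population, those randomized, for both costs and 18-month outcomes. It does not name the data set or imputation rule behind the effect.

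**Cost side.** In Economic outcome measures, the paragraph on resource use and personal costs ends: "These data are obtained at the time of the follow-up assessment". That sentence directly follows the one on personal expenditure and lost work, so its reach is unclear. The same paragraph says clinic contacts are noted for referred patients. The Economic evaluation section adds: "A costing study will record intervention costs (to include staff time, capital, overheads and consumables". The Background refers to questionnaires on "continuity of care and health service use and personal costs are completed at baseline and follow-up".

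**The concern.** An ICER is interpretable only if its cost and its effect describe the same patients under the same assumption about what happened to those not seen. LOCF breaks this here. With two assessments, carrying the last value forward means carrying the baseline forward, and baseline precedes clinic launch. A lost intervention patient therefore contributes zero change to the effect by construction.

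Costs over the following 18 months have no counterpart at baseline. If a baseline service-use questionnaire were carried forward, lost intervention patients would be charged pre-launch costs with no clinic contacts, which is not a usable cost either.

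So if the stated primary result goes into the ICER, the clinics' effect is diluted while their incremental cost is not. The distortion would pass into the acceptability curves and net benefit. The Discussion offers these results to commissioning groups as evidence for adopting the service.

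**Working it through.** **1. Implied loss.** The Sample size section gives no loss rate, but it gives 2,044 retained and at least 2,555 recruited. Then d = 1 − 2,044/2,555 = 0.20, and in reverse 2,044/(1 − 0.20) = 2,555. The plan's figure reproduces.

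**2. Other inputs.** Attainment of all three targets is about 15% at baseline (Primary clinical outcome measure), and 20% in control against 30% in intervention at 18 months (Sample size). The effect E is therefore 10 points. Let C be the mean incremental cost per patient. The article gives no value for it.

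**3. Effect under LOCF, 20% loss in each arm.**
- Intervention: 0.80 × 30 + 0.20 × 15 = 27.0%
- Control: 0.80 × 20 + 0.20 × 15 = 19.0%
- Difference: 8.0 points, that is (1 − d) × E

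**4. Cost.** Under random, equal loss the mean incremental cost is C whether it is taken from attenders or from everyone randomized. The ICER is C/[(1 − d)E] in both cases, so its factor against C/E is 1/(1 − 0.20) = 1.25. With an assumed C of £200, £200/0.10 = £2,000 per extra patient at target becomes £200/0.08 = £2,500.

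**5. Net benefit.** At a threshold λ per extra patient at target, λE − C becomes λ(1 − d)E − C. The shortfall is λdE = 0.02λ per patient.

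**6. If costs were also carried forward.** With balanced baseline costs, C would shrink to (1 − d)C and the ICER would return to C/E. That happens only because lost intervention patients are credited with no clinic cost, and net benefit would still be multiplied by 0.80.

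**7. Sensitivity to assumptions.**
- Loss 25% intervention, 15% control: (0.75 × 30 + 0.25 × 15) − (0.85 × 20 + 0.15 × 15) = 26.25 − 19.25 = 7.0 points; factor 10/7.0 = 1.43.
- Loss 15% intervention, 25% control: (0.85 × 30 + 0.15 × 15) − (0.75 × 20 + 0.25 × 15) = 27.75 − 18.75 = 9.0 points; factor 10/9.0 = 1.11.
- Baseline attainment differing by 2 points, 20% loss: 8.0 ± 0.20 × 2 gives 8.4 or 7.6 points; factor 1.19 or 1.32.
- Non-attenders have a fraction f of the effect and the full incremental cost: the factor is [(1 − d) + df]/(1 − d). With f = 1 it is 1.25, with f = 0.5 it is 0.90/0.80 = 1.125, and with f = 0 it is 1.0.
- Non-attenders have the full effect at no incremental cost, and costs are taken from attenders only: 1/0.80² = 1.56.

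**8. QALYs.** If the baseline EQ-5D is likewise carried forward, a lost patient shows no change and the factor in step 4 applies to cost per QALY under the same assumptions.

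**The case against.** The strongest reply is that nothing in the article explicitly pairs a LOCF effect with attender-only costs. A reader might infer from "These data are obtained at the time of the follow-up assessment" that all costs come from patients seen at 18 months, so that the two halves of the ICER describe different patients. The article does not support that. The sentence may cover personal costs only, clinic contacts and the costing study are not tied to attendance, and the Economic evaluation section names one randomized population for both halves. That reply stands, but it does not remove the problem. By step 4 of the working, the dilution is the same when costs are complete for everyone, because it arises on the effect side.

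A second reply is that the economic section names the outcome measure and not the LOCF data set, that its baseline-to-follow-up comparison would fit patients with both observations, and that a complete-case analysis is planned. This is fair, and it is why the point is conditional. However, LOCF is the only imputation rule stated, the complete-case analysis is secondary, and the ICER is not linked to it.

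A third reply is that a condensed article leaves economic missing-data detail to a fuller plan. Silence on missing costs is indeed no fault. The point rests on a rule that is stated, LOCF for the main analysis, and on a stated output built on the same outcome.

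It is also true that the root cause is LOCF in the primary analysis, and that abandoning it there would largely resolve this point.

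**Conclusion.** The concern holds in conditional form. If the main LOCF result serves as the effect in the ICER, the effect is diluted and the cost difference is not, whether costs come from attenders or from all randomized patients. At the current plan's implied 20% loss, 10 points become 8.0 and the ICER is inflated by a factor of about 1.25.

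That figure is an illustration and not a known bias. It needs equal random loss, balanced baseline attainment, a positive incremental cost and non-attenders who resemble attenders. Loss split 15%/25% between the arms gives 1.11 or 1.43, depending on which arm loses more. If non-attenders incur the cost and truly gain nothing, there is no inflation, but LOCF imposes that case without testing it. The Background hopes for lower care costs and cites one service reported as marginally cost saving. With a negative incremental cost, a percentage inflation of the ICER has no useful meaning, and what remains is the understated effect and net benefit.

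A reader might also take 72 retained of 100 per practice, a 28% loss, and arrive at 1/0.72 = 1.39. Those figures belong to the initial design, which the revised sample size replaced, so they should not be used.

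**What to change.** State in the Economic evaluation section that incremental costs, target attainment and QALYs are all estimated in one common set of randomized patients, with one missing-data method other than LOCF. Joint multiple imputation of 18-month costs, EQ-5D and the three risk factors is one suitable choice, done by arm, using baseline values and respecting clustering by practice. Add a sensitivity analysis restricted to patients with both cost and outcome observed.

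The cost is a change of analysis wording and some extra imputation work. No new data and no further patients are needed.

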#### Qualitative study

All interviews are being audio-recorded with the participants’ consent and later transcribed verbatim. Participants are allocated a study number to ensure confidentiality. Interviews will be analyzed using Framework analysis [49], a systematic and comprehensive method of classifying and interpreting qualitative data particularly concerned with generating policy- and practice-orientated findings [50]. The process will begin with familiarization with the data and identification of both broad and sub-themes, followed by continual reassessment and reinterpretation of these emerging themes and the original transcripts. A ‘framework’ for each theme will be created in which data will be charted against individual participants. This process will retain the original context and quotes, and facilitate exploration of the range of comments made under each theme and the relationships between themes.

## Discussion

The present study will provide a robust estimate of the effects of introduction of intermediate care clinics for diabetes to support the care of patients in UK primary care, and the costs associated with any improvements in outcomes produced. The ICCD model aims to deliver high quality care through a multidisciplinary, locality-based team, with the added opportunity for developing professional expertise in the community. The results of this trial will be of direct policy relevance to the development of diabetes services in the UK, and will provide clinical commissioning groups with evidence to inform decisions on commissioning services to improve control in T2DM. Diabetes and service reconfiguration are both national research priorities but there is an urgent need to base policy on evidence. Modeling suggests the ICCDs will be cost-effective in reducing complications and consequent hospital admissions, as well as producing societal benefits such as reduced incapacity to work. If results from this short-term evaluation are positive they will provide an initial evidence base for adoption and for longer-term evaluations to assess the benefits predicted from modeling. The qualitative study will help identify factors influencing service uptake and, if the trial finds no significant effect, why efficacy was not demonstrated. Forty-nine practices have been randomized and 1,997 patients recruited to the trial. Follow up finished in October 2011 and the results will be available in late 2012. It is not possible at present to comment on the effectiveness or cost-effectiveness of an ICCD service.

## Trial status

At the time of submission, patients were being recruited to the qualitative study, and both follow-up assessments and MIQUEST searches were ongoing.

## Abbreviations

BMI, Body mass index; CHD, coronary heart disease; CRF, Case report form; GP, General practitioner; DTSQ, Diabetes Treatment Satisfaction Questionnaire EQ-5D ,European Quality of Life-5 Dimensions; GPwSI, GP with a special interest; ICC , Intra-class correlation; ICCD , Intermediate care clinics for diabetes; ICERs, Incremental cost-effectiveness ratios; IMD , Index of multiple deprivation; ITT , Intention-to-treat; LOCF , Last observation carried forward; MIQUEST , Morbidity Information Query and Export Syntax; NHS , National Health Service; NICE , National Institute of Health and Clinical Excellence; OR , Odds ratio; PCT , Primary Care Trust; PAID , Problem Areas in Diabetes scale; QALYs , Quality-adjusted life-years; QOF , Quality and Outcomes Framework, a system for the performance management and payment of general practitioners in the National Health Service; T2DM , Type 2 diabetes mellitus; UKADS , UK Asian Diabetes Study; UKPDS , United Kingdom Prospective Diabetes Study.
